### Construct validity

To assess the construct validity of the test the expertise of the participants will be used as an important indicator for knowledge and skills in EBP. It was hypothesized that those with more experience based on theoretical grounds would have higher scores in the test. The scores achieved by the experts will be compared with the scores obtained by the novice group and the intermediate experience group (before test), using an analysis of variance. If a significant difference will be found, a post hoc analysis by Scheffé's method will be added.

Furthermore, residents will be asked to inform their real exposure to EBP measured as number of courses, seminars and conferences have attended and how many hours each course, seminar and conference have comprised. The relationship between the hours of exposure and the score of the test will be assessed by using Spearman's rank correlation coefficient.

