**Item difficulty **(relative difficulty of each item)	% of candidates who answer achieve a passing score	Not given	Ranged from moderate (73%) to difficult (24%); no easy items

**Item discrimination **(ability of each item to discriminate between those with overall high scores and those with overall low scores)	Item discrimination index (ranges from -1.0 to 1.0)	Not given	Ranged from 0.41 to 0.86, no items had negative or weak discriminations

**Construct validity **(evidence that the test measures the construct it intends to)	Mean scores of experts and novices compared by *t *test	Significant difference, higher expert scores than novices	Significant difference, higher expert scores than novices

*Adaptation of Ramos et al[9]

The primary aim of the study is the translation of the Fresno questionnaire into Spanish and its subsequent validation to ensure the equivalence of the Spanish version against the English original.

The specific objectives are: (a) To translate the test into Spanish using the back translation method; (b) To assess the construct validity of the test comparing the scores achieved by tutors with formal methodological training in EBP, the scores of a group of family medicine residents before they have had any formal training in EBP, and finally the scores of a group of family medicine residents with intermediate experience (training) in EBP; (c) To assess the responsive validity (change in knowledge and skills) of the test after a short course in EBP carried out in a group of family medicine residents; (d) To assess the reliability of the test by measuring the internal reliability (degree to which all test questions on the test measure a single construct), the inter-rater reliability (degree to which two scorers rate a single performance similarly), the intra-rater reliability (degree to which onescorer rate a single performance similarly); (e) To assess the feasibility of implementation by reporting the time required administering the test and reporting the time required scoring the instrument.

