## Discussion

Reliability, validity and responsiveness are context-specific attributes, and an instrument that has demonstrated satisfactory measurement properties in one population is not necessarily appropriate for use in other populations.[22] The validation of the Fresno questionnaire into different languages, professional groups, and cultural settings, will enable the generalisability of the test, as well as allowing comparisons between countries and the evaluation of different teaching methods.

Ramos et al. [9] pointed out that there are limitations to the validity, reliability, and general utility of the Fresno test. The reason being the groups they used to develop and validate the test, which probably represented the extremes of proficiency, leaving the middle ground relatively under-represented. The properties of the test may change when it used to assess groups of people that are more representative of the full range of proficiency in EBP. In the present study the inclusion of the group with intermediate experience may represent a wider range of proficiency in EBP. the validation of the Fresno questionnaire into Spanish, in a population with a different background of experience in EBP than the population recruited by Ramos et al [10], will enable the generalisability of the test, as well as allowing comparisons between countries and the evaluation of different teaching methods.[9]

The goals of the instrument include differentiating between people who are knowledgeable and skilled in EBP from those who do not at a point in time (a discriminative instrument) as well as measuring how much knowledge and skills have changed during a period of time (an evaluative instrument). In both cases the instrument must have a high ratio of signal to noise (reliability and responsiveness, respectively) and be valid.

Ramos et al. [9] did not perform an assessment of the responsiveness of the test. In the present study the group of novices, as well as the group of intermediate experience received an educational intervention on EBP about four weeks after completing the pre-test. The last day of the course the test was administered again allowing for the assessment of the responsiveness of the test. Since there are two groups with different experiences it could be expected that the responsiveness would be different, fostering the generalisability of the result.

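### The construct-validity hypothesis is ordered by experience, but the planned ANOVA with Scheffé comparisons is undirected and inefficient for confirming that order

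*Protocol article*

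**What the plan says.** The Construct validity section gives the hypothesis first: "It was hypothesized that those with more experience based on theoretical grounds would have higher scores in the test". Over the three groups that the article defines by experience, this means novice below intermediate below expert.

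It then names the comparison, "The scores achieved by the experts will be compared with the scores obtained by the novice group and the intermediate experience group (before test", and the method, "using an analysis of variance. If a significant difference will be found, a post hoc analysis by Scheffé's method will be added". It names no ordered test or planned contrast, and does not say which pattern of differences would support the hypothesis. Objective (b) in Background compares the same three groups and adds no rule.

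Two other places bear on the point. Table 1 in Background gives the construct-validity result of the original English test as "Significant difference, higher expert scores than novices". The Discussion says that the original groups probably lay at the extremes of proficiency, and continues: "In the present study the inclusion of the group with intermediate experience may represent a wider range of proficiency in EBP".

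**The concern.** The method does not ask the question that the hypothesis poses. The alternative to the F test is any difference among three means, in any direction. Scheffé's method, opened by "If a significant difference will be found", controls error over all possible contrasts. That suits contrasts suggested by the data. It is costly when the few contrasts of interest follow from a hypothesis stated beforehand.

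The cost falls on the adjacent steps. An expert-novice gap is what the original test already showed. What a third group can add is evidence that intermediates score above novices and experts above intermediates. These are smaller differences than the gap between the extremes, and the Scheffé penalty hurts them most. At stake is whether a valid translated test would be shown to discriminate across the range of experience.

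**Working it through.** **Inputs.** The article gives no alpha, SD, group size or expected difference for this analysis, so there is no figure to reproduce. Assumed: alpha 0.05 two-sided, normal scores with a common SD of 1, and novice/intermediate/expert sizes of 30/30/30, 50/50/50 or 150/50/50. The only size in the article is the 202 second-year residents of 2007 (Setting and context).

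**Formulas.** Each adjacent difference is tested by t = (difference in means) / (s × √(1/n₁ + 1/n₂)), with N − 3 degrees of freedom. A planned contrast with an unadjusted 95% CI needs t above t(0.975; N − 3). Scheffé needs t above √(2 × F(0.95; 2, N − 3)).

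**One step by hand, 50 per group, true step 0.5 SD.** The standard error is √(1/50 + 1/50) = 0.20, so the expected t is 0.5/0.20 = 2.5.
- Planned contrast: critical value 1.976, power about Φ(2.5 − 1.976) = Φ(0.524) = 0.70.
- Scheffé: critical value √(2 × 3.058) = 2.473, power about Φ(2.5 − 2.473) = Φ(0.027) = 0.51.

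Both steps together are confirmed less often than the products 0.49 and 0.26, because the two differences share the intermediate mean and are negatively correlated. The joint figures below were simulated (1,000,000 runs per setting).

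**True order, steps of 0.5 SD.**

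| Group sizes | t critical | Scheffé critical | F significant | Both steps, planned | Both steps, Scheffé |
|---|---|---|---|---|---|
| 30/30/30 | 1.988 | 2.491 | 94% | 16% | 4% |
| 50/50/50 | 1.976 | 2.473 | over 99% | 43% | 19% |
| 150/50/50 | 1.970 | 2.463 | over 99% | 57% | 29% |

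With steps of 0.8 SD the joint figures, planned against Scheffé, are 73% and 48%, 96% and 87%, and 98% and 93%.

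**Order false (50/50/50 and 150/50/50; means for novice, intermediate, expert in SD).**

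| Pattern | F significant | Both planned steps | Expert minus novice alone |
|---|---|---|---|
| 0, −0.4, +0.4 (intermediates lowest) | 95%, 95% | 0%, 0% | 51%, 68% |
| 0, +0.5, 0 (experts equal novices) | 73%, 81% | 0%, 0% | 2.5%, 2.5% |
| 0, 0, +0.6 (flat middle) | 88%, 93% | about 1%, about 1% | 85%, 96% |

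The last column also shows why a linear trend contrast with weights −1, 0, +1 should not decide. It gives the intermediate mean zero weight, so it is simply expert minus novice, and it is usually significant when the middle is flat.

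**Multiplicity.** The joint rule needs both one-sided results at 2.5%. If either step is absent or reversed, the rule passes in at most 2.5% of studies, so no adjustment is needed.

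**The case against.** A reader might infer from the order-false table that the plan would declare construct validity in most studies where the order is wrong. The documents do not support that. The article uses F to open the pairwise comparisons and nowhere makes it the criterion of validity. Those comparisons have a sign, the group means will be seen, and intermediates below novices would contradict the hypothesis as written.

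Further points for the plan:
- A condensed article may leave the success rule to a fuller document. That is right, so the missing rule is not counted here as an error. What the article does fix is the method, and that method is a poor match for its hypothesis.
- The comparison sentence sets experts against the other two groups, so the target may be only that experts exceed both. The Discussion says that the intermediate group may widen the range; it does not make intermediate against novice a required comparison. This reading is possible, but it too concerns a few directed contrasts that do not need Scheffé's protection.
- The section has a second, directional analysis: "The relationship between the hours of exposure and the score of the test will be assessed by using Spearman's rank correlation coefficient". Exposure is asked of residents, so it does not test the order of the three groups.
- The joint rule is demanding. This stands: at 0.5 SD steps it misses a true order in 43 to 84% of studies under the assumed sizes. Scheffé misses it more often still.

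**Conclusion.** The point holds as a mismatch of analysis to hypothesis and a loss of power; it is not a route to an undetected false claim. Against Scheffé, two planned contrasts raise the chance of confirming a true order with 0.5 SD steps by about 25 to 28 percentage points at 50/50/50 and 150/50/50 (43 against 19, 57 against 29), and by 12 points at 30 per group (16 against 4). At 0.8 SD steps the gain is 25 points at 30 per group but only 5 to 9 points at the larger sizes. These figures rest on the assumed alpha, common SD, group sizes and step sizes. The direction of the comparison does not, because Scheffé's critical value exceeds the planned one throughout.

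**What to change.** In the Construct validity section, prespecify two directed contrasts on the before-test scores, each with an unadjusted 95% CI: intermediate minus novice, and expert minus intermediate.

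- Claim discrimination across the full range only if both intervals exclude zero in the hypothesised direction.
- If expert minus novice excludes zero in that direction but the adjacent pair does not meet the rule, conclude only that the test separates the extremes.
- Keep the ANOVA and Scheffé comparisons as descriptive support, and do not let a −1, 0, +1 contrast decide.

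If the intended claim is only that experts exceed both other groups, say so and plan those two contrasts in the same way.

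The cost is one rewritten paragraph and a contrast statement in the software already named; no new data are needed. The downside is that the full-range claim is harder to earn than a significant F, and may be missed when steps are modest or groups small.

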### Setting and context

The setting of the study will be the Primary Care Teaching Units in Catalonia (PCTU). At the beginning of the Family Medicine residence program (which longs four years) the medical residents are enrolled into a PCTU. Each PCTU comprises several health centers in a defined geographical area. There are seventeen PCTU in Catalonia.

The number of medical residents in each PCTU ranged from 2 to 52 in 2007. In the year 2007 there were 202 residents in their second year of training.

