### Participants and study description

The instrument will be validated by administering it to a three groups: (a) the first group will comprise by tutors of family Medicine residents with formal methodological training in EBP and who participate regularly in randomised clinical trials conducted in primary care (expert group); (b) the second group will be formed by medical residents in their second year of the Family Medicine training programme in Catalonia, before they have had any formal training in EBP during their residence program (novice group); (c) finally, the questionnaire will be administered to a group of Family and Community Medicine physicians (intermediate experience).

In the present study the group of novices, as well as the group of intermediate experience will receive an educational intervention on EBP about four weeks after completing the pre-test. The last day of the course the test will be administered again allowing for the assessment of the responsiveness of the test. Since there are two groups with different experiences it could be expected that the responsiveness would be different, fostering the expansion of the result.

The following variables will be recorded for each participant: age, sex, year of graduation in medicine, courses in EBP completed prior to the educational intervention and time required in filling-in the test.

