### Administration of the test

To allow the assessment of responsiveness the test will be administered before and after the educational intervention. Repeated administration of measures, particularly those focussing on knowledge, may over-estimate the educational effect and therefore the responsiveness of the test. To minimise the recall bias two sets of test with different scenarios will be prepared. Moreover the pre-test will be administered four weeks before starting the educational module.

Novice and intermediate experience participants will be invited four weeks before starting the educational module to attend a conference about research in primary care and the importance of applying the results of this research into clinical practice. The project of validation the Fresno test will be also presented. The sessions will be decentralised by Health Regions. At the end of each session participants will receive the test (before test). The other test will be administered again on the last day of the course (after test).

The members of the expert group belong to a network of physicians who are regularly engaged in the design and conduct of clinical trials. The network holds in November its annual conference. The members who attended the conference will be asked for filing-in the test. In order to assess the equivalence of the two sets of the questionnaire, both sets will be randomly assigned among the folders distributed to the participants.

In order to assess the feasibility of the test the time required for filling-in the test will be recorded in all cases.

All the participants will be explicitly informed about the research character of the test and that participation was voluntary.

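### With three groups and a significant omnibus test already required, Scheffé's penalty is unnecessary for the pairwise comparisons; a Welch closed test is a cheap improvement

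*Protocol article*

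**What the plan says.** Under Construct validity, the article states an ordered expectation: "It was hypothesized that those with more experience based on theoretical grounds would have higher scores in the test". Expert scores are compared with those of the novice group and "the intermediate experience group (before test), using an analysis of variance". The follow-up is conditional: "If a significant difference will be found, a post hoc analysis by Scheffé's method will be added".

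Participants and study description fixes the number of groups: "The instrument will be validated by administering it to a three groups". Group sizes are left open:
- Novices: Setting and context gives only a pool, "In the year 2007 there were 202 residents in their second year of training", and participation is voluntary.
- Experts: Administration of the test says "The members who attended the conference will be asked for filing-in the test".
- Intermediate: "the questionnaire will be administered to a group of Family and Community Medicine physicians (intermediate experience"), with no number.

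No significance level, power, effect size or SD is given for this comparison, and the variance assumption is not mentioned. The Discussion explains why the third group matters: "In the present study the inclusion of the group with intermediate experience may represent a wider range of proficiency in EBP".

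**The concern.** Scheffé's method protects every possible contrast among the group means. Three groups give only three pairwise differences, and the article already puts an omnibus test in front of them. The extra protection is paid for in power.

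The cost falls mainly on novice against intermediate and intermediate against expert. Those are the comparisons that the intermediate group makes possible, and the article presents that group as widening the range of proficiency beyond the original validation. Expert against novice is a larger gap and is little affected. A non-significant adjacent step might be taken to mean that the Spanish version discriminates poorly when the test procedure was simply too strict.

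A second matter is robustness. The natural reading of an unqualified analysis of variance is the equal-variance form. The groups are chosen to differ in expertise and may well differ in size, so equal spread is not assured.

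**Working it through.** **Inputs.** From the article: three groups; omnibus test first; Scheffé second. Assumed, because the article is silent: 5% two-sided level, normal scores, and the group sizes, gaps and SDs shown below. Sizes and SDs are in the order novice/intermediate/expert. The article has no figure of its own to reproduce.

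**1. Why the penalty is unnecessary.** With means A, B and C, if any two of A=B, B=C, A=C are true, all three means are equal. The only intersection hypothesis above the pairs is therefore the global null, which the omnibus test covers. Rejecting a pair when both the omnibus test and that pair's own 5% test reject is a closed test, with familywise error at most 5% provided that each test holds its level. With the same pooled variance, it also rejects every pair that Scheffé rejects, because a significant Scheffé contrast implies a significant F. As a check (50 per group, two means equal, the third 1 SD higher), the false-positive rate on the equal pair was 4.9% for the closed test and 1.4% for Scheffé.

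**2. Power.** The pairwise critical value under Scheffé is √(2·F(0.95; 2, N−3)). At N = 150 this is 2.473, against t = 1.976 for the unadjusted test.

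For 50 per group and a gap of 0.565 SD, the standardised difference is 0.565·√(50/2) = 2.825.
- Closed test: Φ(2.825 − 1.976) = Φ(0.849) ≈ 80%.
- Scheffé: Φ(2.825 − 2.473) = Φ(0.352) ≈ 64%.

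Simulation (40,000 runs) gives the same 80% and 64%. With sizes 150/50/50 and steps of 0.45 and 0.55 SD, it gives about 78% and 61–62%.

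The loss depends on where the pair sits. With large-sample critical values 1.960 and 2.448, Scheffé power is Φ(z + 1.960 − 2.448), where z is the normal quantile of the closed-test power:

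| Closed-test power | Scheffé loss (points) |
|---|---|
| 30% | 14.4 |
| 50% | 18.7 |
| 60% | 19.3 |
| 80% | 16.2 |
| 90% | 11.4 |
| 95% | 7.4 |
| 99% | 2.3 |

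With 50 per group, a gap of 0.8 SD gives about 93% under Scheffé against 98% under the closed test. At a gap of 1.0 SD the difference is under 1 point.

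**3. Error rate.** Simulated with all means equal:

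| Sizes | SDs | Omnibus F | Scheffé, familywise | Welch closed test |
|---|---|---|---|---|
| 150/50/40 | 1/1.25/1.5 | about 10% | about 8.5% | 5.0% |
| 150/50/40 | 1/0.85/0.7 | 2.3% | about 1.6% | 4.9% |
| 50/50/50 | 1/1.25/1.5 | about 5% | 4.0% | about 5% |

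With 50 per group, Scheffé stayed below 5% for every SD pattern tried, up to a ratio of 2:1. The error exceeds 5% only where sizes differ and the smaller groups are more variable. In that pattern a pooled closed test does worse than Scheffé, because it inherits the full error of the F test (100/50/30 with SDs 1/1.25/1.5: 9.3% against 7.6%). Removing Scheffé and moving to Welch therefore belong together.

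**4. Price of Welch.** With equal SDs, the Welch closed test loses 0 to about 2.5 points to the pooled closed test on adjacent pairs. The loss is largest in small or unbalanced samples. It still beat Scheffé on adjacent pairs in every equal-SD scenario run.

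**The case against.** Analysis of variance followed by Scheffé is recognised, valid under its assumptions, and conservative; preferring another valid method is partly taste. A journal article may also leave variance checks to a fuller plan. Both points stand, and they are why this is not a defect. The post hoc method is nevertheless named in the article, so its suitability can be judged.

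Stronger readings are tempting, and the document does not support them:
- A reader might infer that this study loses 16 points of power. The article gives no sizes, SDs or effects. The groups are chosen to differ in expertise, so the gaps may be wide and the loss slight.
- A reader might infer that the planned analysis breaks its error rate whenever variances differ. It does not with equal group sizes, and it errs on the safe side when the largest group is the most variable. The article states neither the sizes nor the direction of any difference in spread. The 10% and 2.3% above belong to the omnibus F test and not to Scheffé.
- A reader might infer that the change is free. Besides the small loss to the pooled version, simultaneous intervals are given up. Where small groups are more variable, Welch also rejects less often (150/40/25, SDs 1/1.5/2, steps of 0.6: 24.1% against 34.4% for intermediate–expert), although Scheffé's higher rate there comes with an inflated error.
- A reader might infer that a missed adjacent step would count as failed validation. The article sets no such rule, and it has further evidence in the exposure correlation and item discrimination.

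**Conclusion.** This is a cheap improvement and not an error or contradiction. That Scheffé's penalty is unnecessary for pairwise comparisons of three groups after a significant omnibus test follows from the design alone. The size of the gain does not: about 16 points for a pair with 80% closed-test power, about 2 to 19 points over closed-test power of 30% to 99%, and very little for widely separated groups. The robustness gain is conditional. It guards against an error of about 8.5% if the smaller groups are more variable, and against needless conservatism (about 1.6%) if the largest group is, in the scenarios shown. All these figures assume a 5% two-sided level, normal scores, and sizes and SDs that the article does not give.

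**What to change.** In Construct validity, replace the sentence on analysis of variance and Scheffé with wording such as: *The three groups' scores (before-test scores for novices and intermediates) will be compared by Welch's analysis of variance at the 5% level. Only if this is significant, the three pairwise differences will be tested by Welch t tests at 5% each (closed procedure for three groups). Each difference will be reported with a 95% confidence interval, labelled as per-comparison.*

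The cost is a change to the stated method, made before the data are analysed, with no extra participants or measurements. The report should say that the intervals are not simultaneous, and that one may exclude zero when the omnibus test is not significant. If simultaneous intervals matter more to the investigators than pairwise power, keeping Scheffé is defensible, and that reason should then be stated.
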